## **7.7 Statistical Procedures for Microflora Studies**

Microflora measures will be graded on a 0 to 4 ordinal scale and recorded at baseline and post-exposure. Depending on the empirical distributions across the points in this scale, statistical procedures will either involve analysis of the actual pre-post differences (ordinal) or dichotomized versions of the pre and post scores (binary). In the ordinal case, we will use one sample and multi-sample signed rank tests to examine whether (1) there is an overall change in microflora levels and (2) whether the treatment groups differ significantly from each other in pre-post change. Similarly, if dichotomization is more appropriate, then the binary baseline and post-exposure data will be analyzed using exact McNemar tests (to examine if levels change significantly pre to post) and Fisher tests (to examine whether the pre and post prevalence levels differ between groups).

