#### PRN visits

- Any complications that arise may require further clinical evaluation.

**Study Population:** HIV negative men and women with a history of RAI \*

*\*Refers to coitus only, does not include manual stimulation or the use of sex toys or purgatives.*

**Study Size:** A total of 36 participants (12 per treatment group).  
A subset of 9 participants will be assigned to the pK study.

|                           |                                                |            |
|---------------------------|------------------------------------------------|------------|
| Treatment Regimen: | Treatment Stage 1- Study gel administered once | Clinic     |
|                           | Full 7-day recovery period                     |            |
|                           | Up to 3 weeks later:                    |            |
|                           | Treatment Stage 2- Study gel QD x 7 days       | Outpatient |

**Study Duration:** Participant accrual will take approximately 9-12 months and each participant will be on study for approximately 7-14 weeks. The total duration of the study will be approximately 18 months. Specimen and data analysis will require an additional four months.

**Primary Objective:** To evaluate the safety and acceptability of 0.1% and 0.25% UC-781 vaginal microbicide gel versus placebo when applied rectally.

Parameters to be studied include: Frequency of  $\geq$  Grade 2 adverse events  
Acceptability assessments

**Secondary Objective:** To determine whether use of study product is associated with rectal mucosal damage characterized by the following:

Parameters to be studied include: Epithelial sloughing  
Histopathology  
Microflora  
Mucosal mononuclear cell phenotype  
Mucosal cytokine profile  
Mucosal immunoglobulins  
Fecal calprotectin  
Explants- Mucosal cytokine profile and susceptibility to HIV infection

**Tertiary Objective:** To determine the pharmacokinetics of UC-781 vaginal microbicide gel administered rectally in a subset of participants.

Parameters to be studied include:  
UC-781 blood levels to determine absorption from the GI tract

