Rationale: As with vaginal administration of microbicides, there is concern that rectal administration could disrupt the rectal ecology and, therefore, assessments of pre/post exposure-related changes are indicated. Whether rectal administration of drug product will lead to a shift in rectal microflora and whether these shifts will impact health has yet to be determined.

Simon and Gorbach's extensive review of the literature on intestinal microflora describes the concentrations and composition of the gut microflora. Human bacterial concentrations in the colon range from  $10^{11}$  to  $10^{12}$  cfu/ml, with anaerobic bacteria outnumbering aerobes by 1000-fold. The predominant colonic colonizers are Bacteroides, Bifidobacterium, and Eubacterium. Other common colonic organisms are Lactobacilli, Clostridia, Enterobacter, Clostridia, and anaerobic gram-positive cocci. The microflora populations are relatively stable with few qualitative changes along the colonic wall within subjects and are relatively independent of dietary changes.

While the microbiota has more routinely been assessed by culture-dependent methods, other methods have indicated that up to 60-80% of colonic microflora remain undefined by culture. Several microbicide studies assessing microflora ecology have utilized a semi-quantitative microflora assay of swab samples. Patton and Hillier have developed this assay to examine, macaque and human vaginal microflora, as well as the macaque rectal microflora. Of note, when Patton exposed macaques to UC-781 gel rectally, no significant change in the rectal microflora occurred. In order to similarly assess for any shifts in human rectal microflora after exposure to UC-781, a swab sample will be collected at baseline and after the 7-day outpatient exposure.

- Mucosal mononuclear cell phenotype

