#### **4.7 Concomitant Medications**

Concomitant medications are defined as medications taken within 4 weeks prior to enrollment (Visit 2) and throughout the study. Concomitant medications will be permitted with the exception of those prohibited under the inclusion/exclusion criteria. All concomitant medications, including dose changes, will be reported in the source documents and case report forms.

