## 5.2 Visit 2- Enrollment (Week 0)

### 5.2.1 Non-clinical Procedures

- ⊙ Update locator information and remind participant that he or she will receive visit reminders via email and/or telephone.
- ⊙ Provide test results from screening visit and post-test counseling.  
*If any lab abnormalities ≥Grade 2, subject may not proceed with Visit 2. If the investigator feels that the laboratory abnormalities are transient, the lab tests may be repeated within the visit window. If the repeated labs tests are within normal limits, the subject may proceed with Visit 2 at the discretion of the investigator, the DAIDS Medical Officer, the SMC, and the IRB.*
- ⊙ If subject had a positive STI result at Visit 1, the subject will be referred for treatment of that STI. The subject may proceed to enrollment (Visit 2) one week after a CDC-approved (Appendix X) treatment for the STI.
- ⊙ Collect copy of concomitant medication log
- ⊙ Review precautions listed in Section 5.1.1.
- ⊙ Instruct subject in use of CASI for Baseline Behavioral Questionnaire (BBQ).

Eligible participants who are computer literate will be able to respond to the survey either from their homes or using a terminal at one of the researchers' offices.

Participants who are not computer literate will be given a short tutorial on using the computer to answer questions. When the participant feels comfortable, the research assistant will start the CASI program for the participant. The research assistant will remain in the room while the participant answers the questions but will sit so that he does not see the answers being entered. The research assistant will help with computer questions or problems. If a respondent does not understand a question, the research assistant will read the question aloud, referring to a paper copy of the interview and identifying the question by its number.

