## 5.3 Visit 3- (Week 2 +/- 1 week) Single Dose Administration

### 5.3.1 Non-clinical Procedures

- ⊙ Randomize subject and assign participant ID number prior to Visit Day
- ⊙ Provide test results from Visit 2 and post-test counseling.
 

*If any lab abnormalities ≥Grade 2, subject may not proceed with Visit 3. If the investigator feels that the laboratory abnormalities are transient, the lab tests may be repeated within the visit window. If the repeated labs tests are within normal limits, the subject may proceed with Visit 3 at the discretion of the investigator, the DAIDS Medical Officer, the SMC, and the IRB.*
- ⊙ If subject had a positive STI result at Visit 2, the subject will be referred for treatment of that STI. The subject may proceed to Treatment Stage 1 (Visit 3) one week after a CDC-approved (Appendix X) treatment for the STI.
- ⊙ Update locator information and remind participant that he or she will receive visit reminders via email and/or telephone.
- ⊙ Collect copy of concomitant medication log
- ⊙ Review precautions listed in Section 5.1.1.

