## 5.5 Visit 4- (Week 5 +/- 2 weeks) Treatment Stage 2 Clearance

### 5.5.1 Non-clinical Procedures

- If subject had a positive STI result at Visit 3, the subject will be referred for treatment of that STI. The subject may proceed to (Visit 4) one week after a CDC-approved (Appendix X) treatment for the STI.
- Update locator information and remind participant that he or she will receive visit reminders via email and/or telephone.
- Collect copy of concomitant medication log
- Review precautions listed in Section 5.1.1.
- At this time subjects will be given clearance, if applicable, to start the once daily rectal administration of study product the next day and reminded to complete Product Use Log during Treatment Stage 2.
- Give participant Product Use Log, with instructions for proper use.
- Dispense study product and lubricant with thorough instructions for proper use. Instruction will include self-insertion of an empty applicator while a staff member is available to provide guidance.

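### The uncontrolled pre-post microflora test in 7.7 can pick up antibiotic effects as change after gel use; the between-arm comparison should decide

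*Protocol*

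**What the plan says.** **Sampling.** Section 2.1.2 (Microflora) states that "a swab sample will be collected at baseline and after the 7-day outpatient exposure". The laboratory lists in 5.2.3, 5.3.3 and 5.7.3 agree: microflora is swabbed at Visits 2 and 5 and not at Visit 3.

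**Analysis.** Section 7.7 grades microflora from 0 to 4 and poses two questions. The first is whether "there is an overall change in microflora levels". The second is "whether the treatment groups differ significantly from each other in pre-post change". If the scores are kept ordinal, both are answered by rank tests on the pre-post differences. If they are dichotomised, an exact McNemar test addresses change, and Fisher tests compare the arms on prevalence before and after exposure.

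**Treatment during the study.** The infection screen in 5.1.3 is repeated at later visits. After a positive result:
- at Visit 1 (5.2.1): "The subject may proceed to enrollment (Visit 2) one week after a CDC-approved (Appendix X) treatment for the STI";
- at Visit 2 (5.3.1): "The subject may proceed to Treatment Stage 1 (Visit 3) one week after a CDC-approved (Appendix X) treatment for the STI";
- at Visit 3 (5.5.1): "The subject may proceed to (Visit 4) one week after a CDC-approved (Appendix X) treatment for the STI".

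**Other medication.** Section 4.7 says "Concomitant medications will be permitted with the exception of those prohibited under the inclusion/exclusion criteria". None of the 21 exclusion criteria in 3.2 names antibacterials. Section 4.7 has all medication from 4 weeks before Visit 2 onward recorded in the case report forms. Section 7.7 makes no use of that record.

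**The concern.** A participant treated after a positive Visit 1 result can give the baseline swab about a week after treatment, so the later swab may show recovery. A participant treated after Visit 2 or Visit 3 receives the drug between the two swabs, so the later swab may show loss. Antibacterials taken for unrelated reasons are permitted too.

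The first test in 7.7 compares participants with their own earlier swab and has no untreated comparison. It cannot separate gel from antibiotic, or from anything else that happens between the visits. Section 2.1.2 gives the purpose of the swabs as detecting shifts after exposure to UC-781, so a significant overall change invites that reading.

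The binary branch is the weaker one. McNemar is its only test of change, because the Fisher tests compare levels between arms and not change. At stake is a secondary safety-related conclusion that the gel disturbs rectal flora, or part of such a conclusion, when the cause is an antibacterial course.

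**Working it through.** **1. The plan's own figures.** Section 7.7 gives no power or error figure. The only such figures are in 7.4, for adverse events in a group of 12: 1 − 0.8^12 = 0.931 (stated as more than 90%) and 1 − 0.99^12 = 0.114 (stated as 11%). Both reproduce.

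**2. Inputs.** There are 36 participants, 12 per arm (Schema). Section 7.7 states no significance level, so two-sided 0.05 is assumed; 7.6 uses 0.05 for the mucosal parameters. The share r of participants whose flora is shifted in one direction by an antibacterial is not in the documents; 5% to 30% is assumed.

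**3. Changes needed in the uncontrolled test.** With d changes, all in one direction, the two-sided exact McNemar p-value is 2 × 0.5^d. The exact signed rank test gives the same value when zero differences are dropped.

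| d | p |
|---|---|
| 2 | 0.50 |
| 3 | 0.25 |
| 5 | 0.063 |
| 6 | 0.031 |

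Six of 36 participants (17%) suffice with no gel effect.

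**4. Chance of a false signal, all 36 pooled, no gel effect.** The second column is the binomial probability of at least 6 of 36. The third is the simulated rejection rate of the exact McNemar test (20,000 runs) when each participant not shifted by an antibacterial has a 10% chance of loss and a 10% chance of gain, that is, 20% symmetric background change.

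| r (assumed) | At least 6 of 36 | Rejection with background change |
|---|---|---|
| 0% | 0% | 1.7% |
| 5% | 0.8% | 4.5% |
| 10% | 14.5% | 12.5% |
| 15% | 45.9% | 25.3% |
| 20% | 75.4% | 42.9% |
| 30% | 97.8% | 75.9% |

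**5. The randomised comparison.** Fisher's exact test at 12 against 12 gives p = 0.48 for a split of 2 against 0, p = 0.22 for 3 against 0, and p = 0.037 for 5 against 0. With the same r in both arms and no gel effect, it rejects in at most 1.7% of simulated runs over r = 5% to 30%.

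**The case against.** **The controlled comparison is already planned.** Section 7.7 poses the between-arm question alongside the overall one, does not call overall change a gel effect, and does not rank the two. This is fair. But the section does not say which answer governs, and in the binary branch it provides no between-arm test of change.

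**This could be left to a statistical analysis plan.** How concomitant medication is handled often is, and no such plan is at hand. That holds for the sensitivity analysis. It does not hold for the uncontrolled test, which the protocol itself sets as the first question beside visit rules that allow treatment between the swabs.

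**Exposure may be low and partly self-cancelling.** Participants must agree to condoms and to periods of rectal abstinence (3.1). Active rectal infection at baseline is excluded, and criterion 18 in 3.2 gives discretion over prior therapy. A positive herpes result need not lead to an antibacterial. Recovery after a pre-baseline course and loss after a later one pull in opposite directions: six against one gives McNemar p = 0.125. All of this stands and limits the size. Screening discretion does not, however, reach treatment after enrolment, which 5.3.1 and 5.5.1 allow for.

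**The stakes are modest.** Microflora is one of several secondary parameters. That stands.

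**Stronger readings the documents do not support.** A reader might infer that one or two treated participants would distort the between-arm result. Randomisation protects it on average, and a split of 2 against 0 is far from significance. A reader might also infer that two or three treated participants could produce the overall result. That number is not in the documents, and alone it gives p = 0.50 or 0.25. Nor should the main result be confined to participants without antibacterials: this selects on an event that can follow randomisation, shrinks arms of 12, and departs from the intent-to-treat aim in 7.10.

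**Conclusion.** The point holds for the uncontrolled pre-post test. As planned, that test cannot tell a gel effect from an antibacterial effect, and the protocol's visit rules permit antibacterial treatment shortly before the first swab and between the two swabs.

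The size depends on a rate the documents do not give. At an assumed 5% the effect is small: the rejection rate with background change is 4.5%, within the nominal 5%. At about 15% or more it is material, with a rejection rate of 25.3% with background change. These figures assume that every affected participant shifts in the same direction on the same measure, so they overstate the effect if shifts are mixed. The between-arm comparison is affected only by chance imbalance.

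This is an inexpensive improvement to a secondary analysis, not a flaw in the trial's primary conclusions.

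**What to change.** Change 7.7 only:

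1. Keep all randomised participants in the main microflora analysis.
2. Make the between-arm comparison of pre-post change decisive. In the binary case, compare change between arms, or post-exposure status adjusted for baseline, instead of prevalence levels alone.
3. Label the pooled pre-post test (signed rank or McNemar) descriptive.
4. Add a sensitivity analysis that omits or flags participants with systemic antibacterial use from 4 weeks before Visit 2 to Visit 5, using the medication data collected under 4.7, and report it beside the main result.

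No visit, eligibility or treatment rule changes. The cost is a little more analysis and a slightly smaller sensitivity set.

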## **7.8 Statistical Procedures for Explant Studies**

The main question of interest for the explant studies is whether one or both of the UC-781 treatment groups have reduced infectivity post-treatment. As virus growth varies according to the day of observation, comparisons will be made when exponential virus growth ("soft endpoint") is achieved using an improved statistical method developed for the Microbicide Quality Assurance Program (MQAP-NICHD). Optical Density (O.D.) data from all p24 assays will be compared to a universal standard curve for O.D. values within a + 95% confidence interval of the plate standards. Differences between experimental groups will be determined using Repeated Measures ANOVA and ANCOVA (adjusting for baseline differences).

## **7.9 Statistical Procedures for Analysis of Pharmacokinetic Data**

Pharmacokinetics of UC-781 will be evaluated after rectal administration. This will include the UC-781 pK profile of the initial dose (Visit 3) and UC-781 1 day post-QD dose level (Visit 5). The analysis will be performed by investigating plasma concentrations of UC-781 and determining the AUC. Possible UC-781 accumulation will be determined by comparing the median UC-781 AUC on Visit 5 to the median AUC on Visit 3. Maximum concentration of drug ( $C_{max}$ ) and time to reach maximum concentration of drug ( $T_{max}$ ) will be calculated as part of the analysis as stated above.

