### 2.1.2 Secondary Objective

To determine whether use of study product is associated with rectal mucosal damage characterized by the following:

Parameters to be studied include:

- Epithelial Sloughing

Rationale: The sloughing assay is integral to the evaluation of microbicides in the rectum. The only microbicide previously studied in the rectum, is N-9, which led to rapid exfoliation of the rectal epithelium in mice and variable abnormality in humans. A recent study has demonstrated that up to 41% of men who have sex with men (MSM) use vaginal products containing spermicides for lubrication during rectal sex. It is important to have confidence that any microbicide going to market will not have a similar effect.

Using the N-9 example, it is expected that evidence of any injury may be apparent within 15 minutes of exposure to an offending agent. In the case of N-9, substantial reconstitution of these changes occurred by 2 hours and microscopically normal

epithelium was noted after 24 hours. The observation of epithelial sloughing was made by performing a rectal lavage and examining the effluent for epithelial cells. Measurements were conducted using either microscopy, looking for sheets of epithelia, or by counting the cells with a Coulter Counter.

Given the above information, it is best to obtain lavage specimens within the 15 minute –2 hour window after application of a product rectally. Therefore, in this study the first treatment stage will include rectal lavage in order to monitor subjects for epithelial sloughing. Although presence of some epithelial cells in effluent is normal, a dramatic increase from baseline would be concerning. In order to avoid the confounding effects of the standard pre-sigmoidoscopy prep (a hypertonic enema), a Normosol-R pH7.4 (See Appendix XI for package insert) enema will be used instead. Rectal lavage will be performed during the endoscopy at approximately 5 cm. Careful attention will be paid to perform the second lavage at 5 cm to decrease the likelihood of washing the UC-781 off of the mucosa at biopsy sites further up the colon and avoid confounding results caused by a the small amount of KY-like lubricant routinely used during the endoscopy procedure.

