### 2.1.3 Tertiary Objective

To determine the pharmacokinetics of UC-781 vaginal microbicide gel administered rectally in a subset of participants.

Parameters to be studied include:

- UC-781 blood levels to determine absorption from the GI tract

Rationale: UC-781 blood levels will provide some indication of the likelihood of developing resistance to this important class of HIV drugs prior to future trials that may include HIV positive participants.

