## 2.2 Study Design

This is a phase I randomized, blinded, placebo-controlled study of the safety and acceptability of the vaginal formulation of UC-781 gel, when administered rectally, to be conducted in 36 adults (12 per group) residing in the Los Angeles, CA area. All of the participants will be HIV negative. The study design is summarized in the Schema above and the Schedule of Events in Appendix I.

This study will involve 2 stages of treatment. Each treatment stage is independent of the other. **This study aims to examine the effects of 2 different dosing regimens, NOT cumulative toxicity over both stages.** Participants will undergo extensive evaluation during 5 study visits over an approximately 7-14 week period. In addition, acceptability assessments will be completed at baseline and Visit 5.

Interested participants will enter a screening period, which includes (Visit 1) and if necessary a medication washout period. Subjects, who are deemed eligible after this screening period, will return for a baseline evaluation (Visit 2), including clinical evaluation and mucosal specimen collection, as well as a baseline behavioral assessment (BBQ). The BBQ questionnaire will be administered by CASI. Subjects may complete the web-based CASI in the privacy of their own home. If a subject does not have access to the internet, prefers to complete the BBQ at the study site, or requires assistance in using the CASI, they will be accommodated at the study site.

After completing Visits 1 and 2, eligible subjects will be randomized to one of three groups: 0.1% UC-781 gel, 0.25% UC-781 gel, or a placebo gel (12 per group). A subset of 9 subjects (3 from each group) will also participate in a pK sub-study, which will include 6 timepoints (Visit 3- pre, 0.25 hr, 2 hr, 4 hr, Visit 3A- 24 hr, and Visit 5- 1 day post-QD dose draw). During randomization, study staff will be notified if the participant is randomized to the pK sub-study. Subjects will be randomized in blocks of 3, one per group to minimize imbalance in treatment assignments. The first three subjects enrolled in each of three treatment groups will be selected for the pK sub-study. It is possible that participants may refuse to participate in the sub-study, and spots will continue to be offered as needed.

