**If female of child-bearing potential, must confirm HCG negative prior to administration.**
- ⊙ T= 15 min pK draw, if applicable
- ⊙ T= 30 min Collect rectal sponge specimens  
Perform flexible sigmoidoscopy, including:  
Rectal lavage at approximately 5cm  
14 biopsies at approximately 10cm  
14 biopsies at approximately 30cm  
*\* each biopsy measures 8 mm x 2 mm x 1 mm*
- ⊙ T= 2 hr pK draw, if applicable
- ⊙ T= 4 hr pK draw, if applicable  

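### The Visit 3 AUC, Cmax and Tmax are confounded, in an unknown direction, by the lavage and 28 biopsies at about 30 minutes, and Protocol 7.9 and 2.1.3 do not limit their interpretation

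*Protocol*

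**What the plan says.** The tertiary objective (Protocol 2.1.3) names its parameter as "UC-781 blood levels to determine absorption from the GI tract". Its rationale is that "UC-781 blood levels will provide some indication of the likelihood of developing resistance to this important class of HIV drugs", looking ahead to trials that may enrol HIV-positive people.

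Section 2.2 provides that "A subset of 9 subjects (3 from each group) will also participate in a pK sub-study", so six of the nine receive UC-781. It describes the "pK sub-study, which will include 6 timepoints": pre-dose, 0.25, 2 and 4 h at Visit 3, 24 h at Visit 3A, and one draw at Visit 5.

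Section 5.3.2 fixes the order at Visit 3: preparatory enema, gel at time zero, then "T= 15 min pK draw, if applicable", then "T= 30 min Collect rectal sponge specimens". The 30-minute step also includes sigmoidoscopy with a lavage at about 5 cm and 14 biopsies at each of two levels. Blood follows at 2, 4 and 24 h. Times are approximate, but the sequence is called crucial, and no exception is made for the pharmacokinetic subset.

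Section 7.9 opens its account of the analysis with "This will include the UC-781 pK profile of the initial dose (Visit 3" and adds a Visit 5 level. It calculates AUC, Cmax and Tmax, and judges accumulation by comparing the median AUC at Visit 5 with that at Visit 3. It does not mention the lavage or the biopsies.

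**The concern.** A plasma profile describes absorption from a rectal dose only if the dose and the absorbing surface are left alone, or if the disturbance is allowed for when the profile is read. Here both are disturbed after half an hour.

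The protocol recognises each mechanism elsewhere. Section 2.1.2 keeps the lavage low "to decrease the likelihood of washing the UC-781 off of the mucosa at biopsy sites further up the colon"; that precaution protects the biopsies, not the blood profile. Section 1.1 notes that a single cell layer separates the rectal lumen from the lamina propria and links this to systemic exposure. Section 8.3 gives biopsies up to three days to heal, so the 2, 4 and 24 h draws all fall within the healing period.

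Two conclusions are at stake. The first is whether the gel is absorbed and what that implies for resistance. Section 1.2.3 reports no detectable plasma UC-781 after vaginal 0.1% and 0.25% gel, with a quantification limit of 2.5 ng/mL, so undetectable rectal levels are a plausible result. The same section describes another UC-781 trial in which absence of systemic absorption is a condition for dosing HIV-infected women. The second is accumulation: the reference visit is disturbed, whereas the comparison visit follows a week of outpatient doses without lavage or biopsy.

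**Working it through.** **1. Draw count.** From 2.2: pre, 0.25, 2, 4, 24 h and Visit 5 = 6, which agrees with the stated number. The blood volumes in 5.3.3 and 5.7.3 also fit: about 25 ml / 5 draws = 5 ml each, and about 5 ml at Visit 5.

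**2. Position relative to the procedures.** Biopsies: 14 + 14 = 28. Post-dose Visit 3 draws before 30 min: 1 (15 min, itself after an enema). After 30 min: 3 (2, 4 and 24 h).

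**3. What this does to each metric.**
- AUC by the trapezoidal rule (assumed, as 7.9 names no rule) has four segments: 0–0.25, 0.25–2, 2–4 and 4–24 h. Only the first has no post-procedure endpoint.
- Any observed Tmax other than 15 min is a post-procedure time, and the matching Cmax a post-procedure value.
- By the clock, 24 − 0.5 = 23.5 of 24 h (98%) lies after the procedures. This is a share of time, not of AUC or of bias: drug absorbed before 30 min still contributes to later levels.

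**4. Possible size of wash-off.** The documents give no lavage volume, fraction removed or absorption rate, so this is illustration only. Assume first-order absorption at rate ka per hour, linear elimination, and removal of a fraction f of the unabsorbed gel at 0.5 h. The unabsorbed share at that time is exp(−0.5·ka), so

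AUC ratio (disturbed / undisturbed) = 1 − f·exp(−0.5·ka).

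Example: ka = 0.1, f = 0.5 gives 1 − 0.5 × 0.951 = 0.52.

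| f | ka = 0.1 | ka = 0.5 | ka = 1 | ka = 3 |
|---|---|---|---|---|
| 0.25 | 0.76 | 0.81 | 0.85 | 0.94 |
| 0.50 | 0.52 | 0.61 | 0.70 | 0.89 |
| 0.90 | 0.14 | 0.30 | 0.45 | 0.80 |

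**5. Possible effect of the biopsies.** The same model was simulated at the protocol's draw times, with elimination rates of 0.1 and 0.5 per hour (assumed).
- No gel removed, absorption rate doubled after 30 min: sampled Cmax is 1.0 to 1.6 times, and sampled AUC 0.9 to 1.4 times, the undisturbed values.
- Half the gel removed, absorption rate tripled, ka = 0.1: sampled Cmax is 1.03 to 1.07 times and sampled AUC 0.78 to 0.91 times. The two effects can nearly cancel for one metric and not for another.

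**6. Consequence for accumulation.** Suppose a Visit 5 AUC were available and equalled an undisturbed single-dose AUC, so that nothing had accumulated. A Visit 3 AUC at 0.52 of the undisturbed value would give a ratio of 1 / 0.52 = 1.9; at 0.89 it would give 1 / 0.89 = 1.1; at the upward extreme of 1.43 it would give 1 / 1.43 = 0.70. The same true state could look like accumulation or like its opposite.

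**The case against.** The strongest reply is that this is a deliberate trade-off. Section 2.1.2 explains why the lavage must fall between 15 minutes and 2 hours after dosing, and the biopsies serve several secondary endpoints. Pharmacokinetics is tertiary and nested in nine people. That stands, and it is why no change of procedure is proposed. It justifies the sequence, not an interpretation that ignores it.

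Second, the protocol never says that undetectable levels will be read as no absorption, and 2.1.3 claims only some indication about resistance. Also true: the misreading is a risk, not a stated rule. But 2.1.3 offers the levels as the way to determine absorption, and 7.9 sets no limit on that use.

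Third, Visit 5 provides a check after seven outpatient doses, with blood listed ahead of that visit's enema and sigmoidoscopy. This stands in part: it is one level about a day after the last dose, which cannot give an AUC, Cmax or Tmax.

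Fourth, detailed procedures and recording belong in the study-specific manual and case report forms. Recording of times may indeed already be planned there. How the levels are used is fixed in the protocol itself.

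A reader might go further and infer that the profile is cut short, that levels are biased downward, or that 98% of the AUC is distorted. The documents support none of these. Sampling runs to 24 h, so it is the gel's residence and the mucosa that are disturbed. Biopsies could push levels up. The 98% is clock time. Nor do the documents say where the gel lies relative to a lavage at about 5 cm, so how much is removed is unknown.

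**Conclusion.** The point holds as a limit on interpretation. The Visit 3 AUC, Cmax and Tmax come largely from draws taken after lavage and 28 biopsies (3 of 4 post-dose draws, in six participants on active gel). Their bias has unknown sign and size, yet 7.9 and 2.1.3 treat them as describing the initial dose and its absorption. The sequence and the counts come straight from the protocol. Every figure for the size of the bias rests on assumed absorption and elimination rates, removal fractions and biopsy effects. Across the cases examined, the result runs from negligible (fast absorption, little gel removed) to a loss of more than 80% of AUC (slow absorption, 90% removed), with Cmax possibly raised.

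It would be wrong to conclude that the levels carry no information about absorption: a clearly detectable level still shows that drug reached the blood under the study conditions, and the 15-minute and Visit 5 levels are not preceded by lavage or biopsy at the same visit. This is a modest correction to a tertiary objective, worth making because the result feeds a decision about later trials.

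**What to change.** In Protocol 7.9 and 2.1.3:

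- Describe the 2, 4 and 24 h Visit 3 values, and the AUC, Cmax and Tmax derived from that visit, as obtained after about 30 minutes of gel dwell followed by lavage and biopsy, with bias of unknown direction.
- Report the 15-minute Visit 3 level and the Visit 5 level separately, as those not preceded by lavage or biopsy at the same visit. Note that the first follows an enema and the second is a single next-day level.
- State that low or undetectable Visit 3 levels will not by themselves be taken as evidence of no absorption or of low resistance risk.
- State that a difference between Visit 3 and Visit 5 will not by itself be read as accumulation.
- Record the actual times of lavage, biopsies and each draw for the pharmacokinetic participants, if the study forms do not already do so.

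The cost is a few sentences and some recorded times. Procedures, sampling and the secondary endpoints are untouched. The downside is a weaker pharmacokinetic claim.
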